### Sample

One hundred and twenty preterm infants (60/group) will be enrolled. Infants are included if they are less ≤ 32 weeks PMA at birth and parents provide informed written consent. Infants are excluded if they have known gastrointestinal, craniofacial, cardiovascular, neuromuscular, and/or genetic defects. Infants of both genders and all ethnic and racial backgrounds are recruited. We expect approximately 5 % of the sample to be Hispanic and 50 % to be Black/African American. Approximately 10 % of the sample is expected to be multiple gestation (twin or triplet). Two to three infants are enrolled per month; this number is based on data from the clinical setting, our experiences in previous studies, the length of the intervention, and our data collection processes. Infants who are medically unable to transition to oral feeding by 40 weeks PMA are excluded from further study.

Infants are recruited by research nurses who are experienced in neonatal care and trained in study procedures. Initial contact is generally made within 24 to 48 hours after the infant’s birth. A study brochure is provided to parents and a demonstration of study procedures using a doll is given. Parents are encouraged to think about participation for as long as they need; study nurses usually contact parents within 1 to 2 days of first contact to obtain parents’ decision.

A randomization scheme was created by the study statistician for study group assignment using Statistical Analysis Software (SAS 9.3, SAS Institute Inc., Cary, NC, USA). The random group assignments are placed on a card and sealed, only to be used after an infant was enrolled. Once enrolled, infants are randomly assigned to either the intervention or the control group by drawing a card from the assignment set. Parents of twins are allowed to request a single randomization card for both twins or to allow their infants to be randomized independently. Only one twin from a twinset where both infants were randomized with the same card will be included in the analysis.

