#### Power analysis

The proposed sample size for the study is based on associations between measures of feeding experience and components of neurobehavioral development and neurobehavioral organization discovered in our previous studies [18–21]. We anticipate 20 % attrition, primarily for medical conditions that arise or are diagnosed after enrollment. The sample size was determined by assuming each aim will be tested using 2-sided tests at *P* = 0.05. For the primary aim, we expect to detect an effect size of at least 0.7 standard deviation (SD) between groups on the final neurobehavioral score, with at least 90 % power using a 2-group *t*-test. However, a random effects model that takes into account the repeated measurements over time is proposed for the analyses of neurobehavior. Differences of the same effect size should improve the power to at least 95 % because of the additional number of observations. Although we have powered the study to test the primary aim, we also considered power for the additional aims. For secondary aim 1 involving a test of the effect of the intervention on cognitive function at 6 months, the same sample size analysis indicates a 2-unit difference (SD = 3) on cognitive development will be detected with 89 % power with only a 2-group *t*-test; the analysis of covariance (ANCOVA) should have more power. For secondary aim 2, the analyses and the sample size calculations are the same as with the primary aim. Secondary aim 3 will be tested in a manner similar to secondary aim 1 and so the sample size calculations should be similar. For the exploratory aim a sample of 96 infants in a test for zero correlation will provide at least 90 % power to detect *r* ≥ 0.26 and at least 80 % power to detect *r* ≥ 0.21.

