#### Clinical outcomes

Time to full oral feedings, the duration (in days) between the initiation of oral feeding and the achievement of full oral feeding, and length of stay, the number of days between the start of oral feeding and discharge to home, are also measured. Full oral feedings are achieved when the infant is consuming all nutrients orally by breast or bottle without intravenous supplementation or gavage feeding for 24 hours.

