The secondary aims require similar comparisons between study groups on secondary outcomes (cognitive functioning, neurobehavioral development, and clinical outcomes). To test secondary aim 1, differences between the 2 groups on the cognitive outcome measure (BSIDIII cognitive subtest scaled score) at 6 months corrected age will be tested using an ANCOVA with morbidity (NMI) and birth gestation used as covariates. To test secondary aim 2, 4 analyses will be performed, one for each of the feeding-related neurobehavioral outcomes (sucking organization, 2 measures of feeding performance, and HRV). The modeling will be done as above with a repeated-measures mixed-model approach with covariates (birth gestation, morbidity). To test secondary aim 3, separate ANCOVA analyses of the clinical outcomes (time to full oral feeding and length of stay) will be used to compare the 2 groups with the birth gestation age and morbidity covariates.

The intent of the exploratory aim is to identify risk factors of poor neurobehavioral development and cognitive dysfunction in preterm infants. We will test the assumed comparability of randomly assigned groups prior to undertaking further analyses. Secondary analyses will focus on the interactions between risk factors and the intervention differences by first screening the risk factors for effects at *P* = 0.2 and then developing a single exploratory model that includes all of the risk factors that significantly influence the outcome differences between the groups. Additional analyses will focus on the findings for neurobehavioral development including sucking organization and feeding performance, HRV, and clinical outcomes, first by examining the relationships between the risk factors and the components of neurobehavioral development and then by assessing the relationships among the components of neurobehavioral development and the primary outcome measure, the NAPI score (neurobehavioral outcome). The final goal is to identify a model of risk factors, modifiers (measures of neurobehavioral development), and mediators (intervention) that have an effect on the differences between groups.

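### ANCOVA on time to full oral feeding and length of stay uses only infants who reach the event, so secondary aim 3 carries a selection bias of unknown direction and size

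*Protocol article*

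**What the plan says.** The Clinical outcomes section of the protocol article starts both clocks at the first oral feeding. Time to full oral feeding ends when the infant is "consuming all nutrients orally by breast or bottle without intravenous supplementation or gavage feeding for 24 hours". The other outcome is "length of stay, the number of days between the start of oral feeding and discharge to home".

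Under Data management and analysis, the method for secondary aim 3 is fixed: "separate ANCOVA analyses of the clinical outcomes (time to full oral feeding and length of stay) will be used to compare the 2 groups", with birth gestation and morbidity as covariates. The same section says that the intent-to-treat analysis of the all-infants dataset uses the measurements that were obtained, and that illness may stop some infants completing the study. It gives no censoring rule, competing-event rule or assigned value for an infant who never reaches the event.

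The Sample section removes infants medically unable to move to oral feeding by 40 weeks PMA. The Power analysis section states: "We anticipate 20 % attrition, primarily for medical conditions that arise or are diagnosed after enrollment". It carries the power reasoning for secondary aim 1 over to secondary aim 3 without giving an effect or SD in days.

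**The concern.** ANCOVA needs a number of days for every infant it includes, and these outcomes have one only when the event occurs. Once oral feeding has started, the position is:

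| What happens next | Time to full oral feeding | Length of stay |
|---|---|---|
| Death or transfer before either event | no value | no value |
| Discharge home still on gavage | no value | has a value |
| Full oral feeding, then discharge home | has a value | has a value |

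The infants in the first two rows are plausibly those with the poorest feeding course, and whether an infant falls there may depend on the intervention. An analysis confined to infants who reach the event is therefore no longer protected by randomisation, although it is carried out under an intent-to-treat label. At stake is whether the between-group difference in days for two secondary outcomes can be read as an effect of the intervention.

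**Working it through.** **Does another part of the plan repair this?** No.
- The mixed model that allows for missing values is specified for the repeated NAPI scores. Secondary aim 3 has one value per infant and a plain ANCOVA.
- Transformations are allowed for non-normal variables, but they cannot supply a value that does not exist.
- The 40-week rule concerns infants who cannot move to oral feeding, not those who start and then fail to reach the event. It is itself a removal after randomisation.

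**Reproducing the plan's own figure.** Inputs from the protocol:
- Enrolment: "One hundred and twenty preterm infants (60/group) will be enrolled".
- Attrition of 20%, so 120 × 0.8 = 96, or 48 per group. This matches "a sample of 96 infants in a test for zero correlation".
- Two-sided 0.05.
- For secondary aim 1: "a 2-unit difference (SD = 3) on cognitive development will be detected with 89 % power with only a 2-group" t-test.

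Standardised effect = 2/3 = 0.667. Normal approximation: 0.667 × √(48/2) − 1.96 = 3.266 − 1.960 = 1.306, so power is 90.4%. The noncentral t gives 89.8%. The stated 89% is reproduced within rounding. Carried to secondary aim 3, it assumes that all 96 infants have a value.

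**Illustrating the effect of loss.** Assumed, not in the protocol: log-normal times, control median 14 days, log-SD 0.6. The true effect is set at the carried-over 0.667 SD, a log difference of 0.667 × 0.6 = 0.40, or a time ratio of exp(−0.40) = 0.67. The control mean is 14 × exp(0.6²/2) = 16.8 days and the intervention mean is 16.8 × 0.67 = 11.2 days, so the true difference is about 5.5 days. The results below come from simulation. Power is for an unadjusted t-test on log days, starting from 48 per group.

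(A) Infants beyond one long time, common to both arms, never reach the event:

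| Lost, control | Lost, intervention | Difference seen (days) | Effect (SD) | Power |
|---|---|---|---|---|
| 0% | 0% | 5.5 | 0.67 | about 90% |
| 2% | 0.3% | 4.8 | 0.65 | 88% |
| 5% | 1.0% | 4.2 | 0.63 | 85% |
| 10% | 2.5% | 3.5 | 0.60 | 80% |
| 20% | 6.5% | 2.6 | 0.55 | 70% |

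Hand check of the 10% row. The cut-off lies 1.282 SD above the control log-mean, hence 1.282 + 0.667 = 1.948 SD above the intervention log-mean. The mean of a standard normal truncated above at a is −φ(a)/Φ(a), which is −0.195 and −0.061. The log difference seen is 0.6 × (0.667 − 0.195 + 0.061) = 0.32, as simulated.

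(B) Loss unrelated to feeding time (5% or 10%): the difference stays at 5.5 days.

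(C) The same share of each arm's longest times is lost (5% or 10%): 5.0 or 4.6 days. The log difference is unchanged at 0.40.

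(D) More of the longest times are lost from the intervention arm (control 5% against intervention 10%, or 2% against 10%): 5.6 or 6.5 days. With no true effect, the same losses give a false benefit of 1.0 or 1.9 days.

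**The case against.** The strongest defence is that handling of infants without an event commonly sits in an analysis plan, which is not shown, and that the protocol is open about analysing the measurements obtained. Nothing in these sections is contradictory or arithmetically wrong. This stands as far as detailed rules go. It does not answer the point, because the protocol does more than stay silent: it names ANCOVA for outcomes that exist only once an event has occurred.

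A reader might infer three stronger things that the protocol does not support:
- **That both outcomes are missing for an infant sent home on gavage.** That infant has been discharged home and so has a length of stay.
- **That the ANCOVA necessarily shrinks the effect.** This needs an effective intervention and heavier loss of slow feeders from usual care. Scenario A builds that in through its common cut-off; B and D show that the bias can be nil or run the other way.
- **That a definite loss of power can be quoted.** The protocol gives no rate of death, transfer or discharge on gavage. The 48 per group is already net of 20% attrition, mainly medical, so removing more infants may count some twice. The exclusions for known defects and the 40-week rule may also remove some of them. The illustrations omit the planned covariates.

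An infant who never starts oral feeding has no time zero for either outcome, so no analysis of these endpoints as defined can include every randomised infant.

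**Conclusion.** The point holds as a selection problem on two secondary outcomes. The stated ANCOVA compares only infants who reach full oral feeding or discharge home, which is conditioning on a post-randomisation outcome. The protocol does not allow the direction or size of the bias to be determined. Under the stated assumptions the difference seen ranges from 2.6 to 6.5 days against a true 5.5. In the scenario that favours shrinkage, power falls from about 90% to between 88% and 70% as control loss rises from 2% to 20%. The possibility of a false benefit of 1.0 to 1.9 days under no true effect matters at least as much as the loss of power. The primary aim is unaffected. The change should be made, but it is not critical to the trial.

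**What to change.** Replace the ANCOVA as the main analysis of secondary aim 3 with a time-to-event analysis of all infants who start oral feeding:
- Death is a competing event for both outcomes.
- Transfer or loss to follow-up is censored at the last known date.
- Discharge home on gavage counts as full oral feeding not attained; for length of stay it is an event.
- Birth gestation and morbidity stay as covariates, as already specified.
- The number and proportion reaching each event are reported by group, together with the number who never start oral feeding.
- The ANCOVA among infants who reach the event is kept as supportive.

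The cost is a change of wording and a standard procedure in SAS, which the protocol already names. The clinical outcomes come from the health record, and no new data collection or change of sample size is apparent. The protocol lists the trial as still recruiting. The downside is small: the result is a hazard ratio or cumulative incidence rather than a mean difference in days.

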Our intervention, a patterned feeding experience (PFE), is not currently used in most neonatal settings. The intervention is based on principles of neural plasticity and neuroprotection and is designed to take advantage of neuronal synaptic development and both experience-expectant and experience-dependent characteristics of the developing brain [13]. In addition, the intervention takes advantage of a regularly occurring caregiving and life-sustaining event in the life of an infant–feeding. The PFE intervention involves a continuity of tactile experiences associated with feeding to train and build neuronal networks supportive of the normal experience. There are virtually no accepted and no tested caregiver behaviors related to enteral feedings in preterm infants, although some recent research has produced evidence for a positive effect of greater caregiver sensitivity to the infant during feeding [14]. Theoretically, our intervention provided at a critical time in neurologic system development and associated with a recurring event such as feeding should enhance neural connections that may be important for later development, particularly language and other cognitive and neurobehavioral organization skills [15].

The overall objective of this study is to test the effect of a PFE from birth to NICU discharge for infants born at 32 weeks gestation and younger. The primary aim of the study is to test the effect of a PFE on neurobehavioral organization at 3 time points: the transition to oral feedings, NICU discharge, and 2 months corrected age (48 weeks PMA). Secondary aims are to test the effect of a PFE on 1) cognitive function at 6 months corrected age; 2) neurobehavioral development; and 3) clinical outcomes including time to first oral feeding, time to full oral feeding, and time to discharge. An exploratory aim is to describe the potential effects of perinatal and infant risk factors including immunologic and genetics influences on the outcome variables (neurobehavioral organization, cognitive function, neurobehavioral development, and clinical outcomes). We hypothesize that infants who receive the PFE will have improved neurobehavioral organization, cognitive function, neurobehavioral development, and clinical outcomes compared to infants who receive usual feeding care in the NICU.

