#### Neurobehavioral development

Both CNS development and autonomic nervous system (ANS) function are measured as indicators of neurobehavioral development. Sucking organization (suck bursts/feeding, burst duration, interburst interval) is a reliable measure of CNS function [30]. In addition, oral feeding performance (proportion consumed, efficiency) is a reliable indicator of CNS integrity [31]. These measures are taken during twice weekly observation feedings during Phase 2 of the intervention or, for infants in the usual care group, once oral feedings have started. To measure sucking, a noninvasive, piezoelectric sensor is placed on the infant’s jaw where it detects movements associated with sucking. A computer data acquisition system based on the Biopac Systems MP-150® data acquisition system is used to collect and store data (BIOPAC Systems, Inc, Goleta, CA, USA). Software developed by our team allows extraction and processing of the data from the acquisition file using algorithms developed by us.

Feeding performance consists of two measures: proportion consumed and efficiency. These measures have been reliably used in numerous feeding studies [32–34]. Proportion consumed, which incorporates both oral-motor skill and level of endurance, is the percent of prescribed formula or breast milk consumed over the feeding time, not counting breaks for burping or rest. The amount consumed is recorded at the end of the feeding. Efficiency refers to the total volume taken over feeding time and is a reflection of oral-motor skill as well as fatigue. The amount taken is recorded by the study nurse at the end of the observation feeding. Feeding time is calculated by the data acquisition system and eliminates non-feeding times (that is burping or rest breaks).

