Heart rate variability (HRV) is a measure of ANS maturation and an indication of infant well-being and development [35, 36]. HRV increases with increasing PMA and, as the infant is more able to control breathing, an increase in parasympathetic activity occurs, as seen in the high frequency (HF) power spectrum of HRV. Both parasympathetic and sympathetic activity is seen in the low frequency (LF) power spectrum. Higher respiratory rates and activity result in a higher LF:HF ratio, consistent with a stress model. HRV effects have been found to be associated with poor autonomic organization during feedings. We examine HRV twice a week during observation feedings with data collected by the acquisition system described above. The electrocardiogram waveform is sampled at a rate of 1000 samples/second; the instantaneous R-R time interval is used for computation of HRV after being digitally filtered to remove artifact. HRV includes the LF and HF proportions (in normalized units) and the LF:HF ratio.

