#### Randomization to groups

A random assignment scheme was developed by the study statistician using a random number generator. Infants are assigned to groups at enrollment in equal numbers using 120 cards marked with one or other group contained in sealed envelopes and kept in a locked cabinet in the study office. Assignment to group is not blinded to parents, NICU staff, or the study nurses. The examiner for the major study outcomes is blinded to group assignment.

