## Discussion

This study is a randomized trial to test the effectiveness of a theoretically derived, neuroprotective intervention for preterm infants developed to be easily incorporated into the context of routine NICU care. The effect of the intervention on preterm infant neurobehavioral organization, cognitive development and neurodevelopment as well as on clinical outcomes will be measured. We will also assess the potential effect of various risk factors on the neurodevelopmental outcomes and as potential moderators of intervention effectiveness. The results of the study have the potential to change neonatal feeding practices, which currently do not systematically support infant neurologic development. Moreover, the study results are potentially applicable to other groups of hospitalized infants including those requiring surgery shortly after birth.

The intervention has several strengths including its strong theoretical link to experience- dependent neural development. The intervention costs little and is easily implemented in a busy NICU. Moreover, the intervention can be provided by family members, nurses and other care providers with minimal training, making its implementation and long-term sustainability more likely.

Study results will be reported to participating study settings, the National Institutes of Health, professional organizations via investigator presentations, and to the scientific and lay public via journal publications.

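### The exploratory aim's closing sentence misassigns causal roles: Phase 2 measures that PFE is expected to change are called modifiers, and the randomised intervention a mediator

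*Protocol article*

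**What the plan says.** The final sentence of Data management and analysis sets the goal of the exploratory work as "a model of risk factors, modifiers (measures of neurobehavioral development), and mediators (intervention) that have an effect on the differences between groups". The other relevant statements in the protocol article are these:

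- **Assignment** (Randomization to groups): "Infants are assigned to groups at enrollment in equal numbers using 120 cards".
- **Timing of the measures** (Neurobehavioral development): on sucking and feeding performance, "These measures are taken during twice weekly observation feedings during Phase 2 of the intervention"; on heart rate variability, "We examine HRV twice a week during observation feedings".
- **Expected effect** (Background): the hypothesis is that "infants who receive the PFE will have improved neurobehavioral organization, cognitive function, neurobehavioral development, and clinical outcomes" compared with usual care.
- **Status of the measures** (Data management and analysis): "The secondary aims require similar comparisons between study groups on secondary outcomes (cognitive functioning, neurobehavioral development, and clinical outcomes").
- **Moderators** (Discussion): the plan is to assess the potential effect of "various risk factors on the neurodevelopmental outcomes and as potential moderators of intervention effectiveness". The only interaction step described in the analysis section also uses risk factors, screened at P = 0.2.

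**The concern.** A modifier is a characteristic across whose levels the treatment effect differs. It should be fixed before treatment or be unaffected by it. A mediator lies between treatment and outcome. The closing sentence gives the first role to variables that the trial expects treatment to change, and the second role to the treatment itself.

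The labels matter because they guide which variables receive group-by-variable terms and which are analysed for direct and indirect effects. An analyst who followed them would present treatment-affected outcomes as effect modifiers. The mechanism question raised by the trial's theory, whether PFE works through better feeding organization, would have no analysis aimed at it.

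**Working it through.** The plan states no figure on this point, so there is nothing to reproduce. The check has two parts.

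**1. Roles side by side**

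| Variable | Role in the closing sentence | Role implied elsewhere in the article |
|---|---|---|
| PFE or usual care | mediator | exposure: it defines the two randomised groups |
| Sucking, feeding performance, heart rate variability | modifiers | candidate mediators: recorded after assignment, hypothesised to improve, tested as secondary outcomes |
| Risk factors | listed without a moderator role | moderators (Discussion and the interaction step) |

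The gap between assignment and measurement is not trivial. Enrolment is in the first week of life, and the Intervention section says that Phase 1 can last as long as 12 weeks before oral feeding begins.

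**2. What conditioning on such a measure does**

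Let T be the arm (0 or 1), M a Phase 2 measure, Y the NAPI score and U an unmeasured cause of both. Assume M = aT + uU + error and Y = bM + uU + error, with error SD 1, no direct effect of T and no true effect modification. Then:

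- total group difference = a × b
- within-arm slope of Y on M: s = b + u²/(u² + 1)
- arm coefficient once M is in the model = ab − a × s = −a × u²/(u² + 1)

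The article gives none of a, b or u. The values below are assumptions, and results are in units of the error SD, not NAPI points. The simulations used 96 infants (120 × 0.8, the number in Power analysis), 4000 runs each, fitting Y on T, centred M and T × M.

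| Scenario | a | b | u | Total | Arm coefficient by formula | Simulated (significant) | Simulated T × M (significant) |
|---|---|---|---|---|---|---|---|
| A: fully mediated, no shared cause | 0.7 | 0.5 | 0 | 0.35 | 0 | 0.00 (5%) | 0.00 (5%) |
| B: fully mediated, shared cause | 0.7 | 0.5 | 1 | 0.35 | −0.7 × 0.5 = −0.35 | −0.35 (27%) | 0.00 (5%) |
| C: no effect on Y, shared cause | 0.7 | 0 | 1 | 0 | −0.35 | −0.35 (27%) | 0.00 (5%) |
| D: as C, and PFE narrows the error SD of M to 0.4 | 0.7 | 0 | 1 | 0 | −0.48 | −0.48 (49%) | 0.37 (44%) |
| E: PFE leaves M unchanged | 0 | 0.5 | 1 | 0 | 0 | 0.00 (5%) | 0.00 (5%) |

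In D the slopes differ by arm: 1/(1 + 1) = 0.50 under usual care and 1/(1 + 0.16) = 0.86 under PFE. The spurious interaction is therefore 0.86 − 0.50 = 0.36. The arm coefficient, taken at the overall mean of M (0.35 from each arm mean), is −0.35 × (0.50 + 0.86) = −0.48.

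Three results follow. In A the arm coefficient is a correct direct effect of zero, but it is not the effect of PFE, which is 0.35. In B, C and D it is biased even as a direct effect. The interaction term is false only in D.

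**The case against.** **No model is written out.** The article states a final goal. It gives no group-by-measure term, adjustment set or mediation method for the Phase 2 measures, and an article may leave model form to a fuller document. The only interaction step uses risk factors, so the sentence may be a simple swap of terms. This stands against the stronger reading a reader might infer, that the plan as written yields biased estimates of effect modification. The documents do not support that: nothing runnable is specified, and in the scenarios above the interaction term was wrong only when PFE also changed the spread of the measure. It does not remove the point, because a wrong role that is stated is not the same as a detail left out.

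**A smaller coefficient is not in itself bias.** If a 0.70 SD effect is half mediated and there is no shared cause, the coefficient given the measure is 0.35 SD, which is the correct direct effect. Setting its power (about 45% against 92%) beside that of the total effect compares two different quantities. This stands, and no loss of power is claimed here.

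**Intervention might mean the delivered dose.** The Intervention section records attended feedings as a dose covariate, and Usual care records tactile exposure in controls. Delivered dose follows assignment and could be an intermediate variable. The sentence does not say dose, and this reading would not rescue the label on the Phase 2 measures.

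**The Discussion does not say baseline.** This is correct. It names risk factors without restricting their timing, and it gives the Phase 2 measures no role. The restriction to factors fixed before randomisation is a recommendation. It is needed because the listed risk factors include late cranial ultrasound at 34 to 36 weeks PMA.

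**Mediation analysis has the same weakness.** A direct effect from a mediation model also conditions on M, so an unmeasured shared cause biases it too. This stands, and the assumption has to be declared.

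**Conclusion.** The closing sentence misassigns roles and conflicts with the hypothesis in Background, with the status of the same measures as secondary outcomes, and with the moderator role given to risk factors in the Discussion and in the interaction step.

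If the final exploratory model follows the labels, its account of what modifies the group difference can be uninterpretable. Its group coefficient would then be a direct effect conditional on a consequence of treatment, not the effect of PFE. That coefficient is also biased if an unmeasured cause drives both the measure and NAPI. Such a cause is plausible, since the article itself says that severity of illness distinguishes infants' neurobehavioral performance. Both consequences depend on PFE changing the measures, as the trial hypothesises; with no such change (scenario E) neither arises.

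No magnitude can be fixed from the documents; the simulated figures only illustrate assumed values. The primary NAPI comparison and the secondary comparisons are unaffected, so the point is confined to an exploratory aim.

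**What to change.** Restate the closing sentence with these roles:

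- **Exposure:** randomised group.
- **Candidate moderators:** risk factors measured before or at randomisation, tested as group-by-factor terms. Genotype qualifies although saliva is collected later, because treatment cannot change it. Findings that arise after assignment, such as the late ultrasound, do not qualify.
- **Candidate mediators:** the Phase 2 sucking, feeding-performance and heart rate variability measures. Keep them out of the moderator model and examine them in a separate exploratory mediation analysis of direct and indirect effects, adjusted for birth gestation and morbidity, with the no-unmeasured-confounding assumption stated.

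If delivered dose was meant by intervention, say so and define it separately from assignment.

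The cost is one rewritten sentence and one extra exploratory analysis, with no new data. The downside is that the mediation analysis rests on an assumption that the trial cannot test, so its results should be reported as exploratory.
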